### Discontinuation criteria

Statement by the participant or their legal representative requesting discontinuation of participation in this study. Or adverse events, symptoms, and signs of toxicity at the investigator’s discretion. Or any condition in which, in the opinion of the investigator, it would be advantageous for the participant not to comply with the procedures specified in this protocol and by the sponsor’s request. In case of premature discontinuation, a clinical visit will be conducted, and the same date of the last visit (6-month) will be collected.

An Independent Data Safety Monitoring Board of academic physicians not associated with the study sponsor will provide data and safety adjudgment. A Clinical Events Classification Committee will give a blinded adjudication of clinical events.

## Study endpoints

### Primary safety outcome

It is a combination of serious adverse events (SAEs) accumulated within 6 months of insertion of the gestrinone or placebo pellet and collected through spontaneous reports and clinical findings. The primary safety outcome will be the percentage of patients who do NOT experience SAEs 6 months after randomization.

SAEs are unfavorable medical events that result in any of the following outcomes:DeathThreat or risk to lifeNeed for hospitalizationProlongation of pre-existing hospitalizationPermanent disability or damageCongenital anomaly; orSignificant medical occurrences that, based on appropriate medical judgment, may harm the participant and require medical or surgical intervention to prevent any of the other occurrences mentioned. In this study, the occurrence of thromboembolic events (such as, for example, acute myocardial infarction, pulmonary embolism, deep vein thrombosis, ischemic stroke, and transient ischemic attack) was pre-defined as a significant medical occurrence.

### Secondary safety outcomes [timepoints: pre-pellet insertion assessment, 3 and 6 months after gestrinone or placebo pellet insertion]

The main secondary safety outcome will be defined as the number of participants who experience androgenization defined by:Hirsutism: defined by Ferriman-Gallwey Score ≥ 8Clitoromegaly: defined by Clitoral index ≥ 35 mm^2^Acne: defined by the IGA scale (Investigator’s global assessment) grade 5 – severe inflammatory acne dominates the area, and there are many comedones, pustules, papules, and cystic acneAlopecia with sequelae of scalp thinningDeepening of the voice

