#### Side effects

Most of the adverse effects of gestrinone are due to its androgenic activity and include acne, skin and hair seborrhea, mild hirsutism, edema, weight gain, voice changes, androgenetic alopecia, and clitoral hypertrophy. The drug showed an embryotoxic effect on animals, with a risk of androgenization of female fetuses. It reduces HDL concentrations, and it is recommended to monitor cholesterol and liver transaminase levels in hyperlipidemic patients and glucose levels in diabetic patients. Other effects related to inhibition of the pituitary-ovarian axis may include menstrual disorders and amenorrhea, hot flashes, sweating, breast reduction, changes in libido, vaginal dryness, and emotional fluctuations [13].

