3. Other medical or psychiatric conditions, including recent laboratory abnormalities (within the last 12 months) that may increase risks to the study participant or, at the discretion of the investigator, make the participant inappropriate for the study
4. Personal history of thromboembolic events
5. Use anticoagulant medication
6. Contraindication to the use of hormonal contraceptives
7. Suspected or confirmed pregnancy
8. Breastfeeding
9. Current or recurrent pelvic inflammatory disease or other conditions that increase the risk of pelvic infections
10, Postpartum endometritis or septic miscarriage in the last 3 months
11. Abnormal uterine bleeding of unknown etiology
12. Congenital or acquired uterine anomalies, including fibroids (leiomyomas or fibromas) that cause distortion of the uterine cavity
13. Uterine or cervical malignancy
14. Suspected or confirmed diagnosis of estrogen-dependent neoplasm, including breast cancer
15. Cervicitis or vaginitis, including bacterial vaginosis or another uncontrolled lower urinary tract infection
16. Cervical dysplasia
17. Active liver disease or dysfunction
18. Benign or malignant liver tumors
19. Allergy or intolerance to levonorgestrel, gestrinone or any other ingredient or component of the Kyleena^®^ formulation or hormonal pellets
20. Previously inserted intrauterine device or levonorgestrel-releasing intrauterine system that has not been removed
21. History of recent trophoblastic disease and continued high HCG levels
22. Bacterial endocarditis
23. Hyperandrogenism at the time of randomization, defined by: hirsutism: Ferriman-Gallwey score ≥ 8; clitoromegaly: defined by the Clitoral index ≥ 35 mm^2^, acne: defined by the IGA scale (Investigator’s global assessment) grade 5 – severe inflammatory acne dominates the area and there is a large number of comedones, pustules, papules and cystic acne; alopecia with sequelae of scalp thinning
24. Diagnosis of polycystic ovary syndrome
25. Participation in another pharmacotherapeutic or investigational medical device study within 30 days prior to the start of study treatment
26. Tobacco Use
27. Use of testosterone-derived hormones and analogues in the last month

Potential participants will be recruited by publicizing the study by doctors in their clinics, through social media, and the Science Valley Research Institute website in the study tab by answering a volunteer questionnaire. All the materials for recruitment purposes will be approved by the local IRB.

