### Deepening of the voice

A speech therapist will evaluate the participant’s vocal pattern using protocols and equipment validated by evaluating professionals. The participant’s voice will be recorded using a digital recorder for evaluation. The pattern observed on each visit will always be compared with that recorded during the initial visit (Basal) to detect possible vocal changes and, more specifically, the deepening of the voice.

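### The androgenization outcome counts hirsutism, clitoromegaly and acne only when the entry cut-off is crossed, so the size of worsening is ignored and new grade 4 acne on clear skin is not an event

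*Protocol article*

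**What the plan says.** Under Secondary safety outcomes the article sets the main secondary safety outcome as the "number of participants who experience androgenization defined by" five criteria, assessed before insertion and at 3 and 6 months. These are a Ferriman-Gallwey score of at least 8, a clitoral index of at least 35 mm², IGA acne grade 5, alopecia with scalp thinning, and deepening of the voice.

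Table 1, exclusion criterion 23, uses the first four in the same form to keep women out: "Hyperandrogenism at the time of randomization, defined by: hirsutism: Ferriman-Gallwey score ≥ 8; clitoromegaly: defined by the Clitoral index ≥ 35 mm^2", then "acne: defined by the IGA scale (Investigator’s global assessment) grade 5", then "alopecia with sequelae of scalp thinning".

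Only voice is tied to the participant's own starting point: "The pattern observed on each visit will always be compared with that recorded during the initial visit".

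The Side effects section says: "Most of the adverse effects of gestrinone are due to its androgenic activity and include acne". Acne heads that list, and mild hirsutism is also on it.

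Statistical analysis compares scores and indices with baseline by paired t-test and Wilcoxon test, and compares changes in other secondary outcomes by paired Wilcoxon test. It also promises descriptive summaries by treatment group for all study variables.

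**The concern.** The secondary safety objective is to evaluate the potential of the pellet for androgenization. An outcome that registers only the crossing of a fixed line answers that in part. It cannot tell a small change near the line from a large one, and it records nothing for a large change that stops short of it.

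The lines also sit at different severities. Acne must reach the worst grade of its scale, while hirsutism counts from 8, which the Hirsutism section places in its mild band (8 to 15) on a scale of 0 to 36. The headline count could therefore show little or no acne even if many treated women developed marked new acne.

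**Working it through.** The document gives no event rate, power or sample-size figure for this outcome, so there is no stated figure to reproduce. The check applies the written rules to cases.

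**1. Rule check.** Entry rule: exclude if Ferriman-Gallwey ≥ 8, clitoral index ≥ 35 mm², IGA grade 5, or alopecia with thinning. Event rule: the same four, or voice deepening. Each woman below meets none of the other criteria.

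| Course from baseline | Eligible at entry | Event |
|---|---|---|
| Acne, grade 0 to 4 | yes | no |
| Acne, grade 4 to 5 | yes | yes |
| Ferriman-Gallwey, 0 to 7 | yes | no |
| Ferriman-Gallwey, 7 to 8 | yes | yes |
| Clitoral index, 15 to 34 mm² | yes | no |
| Clitoral index, 34 to 35 mm² | yes | yes |

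For acne, a rise of up to 4 of the 5 possible steps from clear skin goes uncounted. The article describes grade 4 as more visible inflammatory and non-inflammatory lesions, possibly with cysts.

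**2. Do the baseline comparisons fill the gap?** A paired test compares each woman with herself. It does not alter who is counted and does not set gestrinone against placebo. Both arms also receive the levonorgestrel device, so change within an arm cannot be assigned to the pellet without the between-arm contrast.

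**3. Hirsutism near the cut-off.** The document gives no rater error, so this step rests on assumptions. Suppose the reading is the true score plus a normal error, rounded to an integer. Then P(reading ≥ 8) = 1 − Φ((7.5 − true score)/SD), and for two visits with independent errors the chance of at least one such reading is 1 − (1 − p)².

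- True score 7, SD 1.0: p = 1 − Φ(0.5) = 0.309; over two visits 1 − 0.691² = 0.52.
- True score 7, SD 1.5: p = 1 − Φ(0.333) = 0.369; over two visits 1 − 0.631² = 0.60.
- True score 6, SD 1.0 to 1.5: over two visits 0.13 to 0.29.
- If the error is instead a stable offset of one investigator, a stable woman read below 8 at entry stays below 8, and the probability is 0.

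For a true score of 7 the range is therefore about 0 to 0.60. How many women will sit at 6 or 7 is not known.

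**4. Cut-off wording.** The outcome uses at least 8 and at least 35 mm². The Hirsutism section puts the sign of androgen excess above 8, yet starts mild hirsutism at 8. Clitoris measurement requires an index above 35 mm² together with diameters above 6.5 and 4.4 mm. A score of exactly 8, or a 7 × 5 mm measurement (7 × 5 = 35 mm²), is an event under one wording and not under the other.

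**The case against.** Matching the entry and endpoint criteria is a recognisable incident-case design. A reader might infer from the shared cut-offs that women already androgenized at baseline will be counted. The document does not support that: exclusion criterion 23 removes them, so any event in a correctly enrolled woman is a new onset. Alopecia is a presence criterion and, given the exclusion, already means new alopecia. This stands, and it limits the point to the size of worsening in the three graded components.

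A reader might also infer that an acne signal would vanish from the trial. It would not. Adverse events and all androgenization items are assessed at all three visits, and summaries by arm are promised for all variables. Sub-threshold acne could be seen there, but the main secondary outcome would still not register it.

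A third tempting inference is that the definition makes the pellet look safer overall. Missed acne lowers the count. False hirsutism events, if similar in both arms, dilute the contrast but raise the gestrinone count. The net direction on the reported number is not established.

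Finally, any binary endpoint discards degree, and further tabulations may sit in an analysis plan not shown. That is fair for the detail. It does not change the stated definition, which sets acne at the top grade for an effect the article itself expects.

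**Conclusion.** The point holds for hirsutism, clitoromegaly and acne, and is strongest for acne. Under the stated rule, new grade 4 acne on clear skin is not an event, and the planned paired tests do not compare worsening between arms. This follows from the text alone and needs no assumption.

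The hirsutism misclassification is possible but not quantified. The upper figures of 0.52 to 0.60 require a true score of exactly 7, a rater SD of 1.0 to 1.5 and errors independent between visits, none of which the document gives. The differing cut-off wordings are a separate, definite inconsistency.

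The consequence is a main secondary outcome that answers the androgenization objective incompletely. It does not invalidate the count.

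**What to change.** Keep the androgenization count as defined. Beside it, report a between-arm analysis of worsening from each participant's own baseline for IGA grade, Ferriman-Gallwey score and clitoral index at months 3 and 6. Suitable forms are shift tables and change from baseline by arm, plus the proportion with a pre-set rise in IGA grade. The document offers no basis for that margin, so the investigators should choose and justify it.

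Replacing the component definitions outright is not advised. The last visit was estimated for April 2025 and the article is dated July 2025, so a redefinition now risks being a post hoc change. The added analysis should itself be fixed before unblinding or, failing that, labelled post hoc.

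Reconcile the at-least wording for hirsutism and clitoral index in the outcome and in exclusion criterion 23 with the greater-than wording, and the added diameter limits, in the Hirsutism and Clitoris measurement sections.

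The cost is a little more analysis. No new data are needed, since Assessment of outcomes measures schedules these evaluations at all three visits. The androgenization result may turn out less favourable.

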### Other secondary safety endpoints [timepoints: pre-pellet insertion assessment and 3 months after gestrinone or placebo pellet insertion]

The number of participants who experience:Laboratory values outside the reference range and clinically relevant for serum hormone concentrations (total testosterone, free testosterone, and SHBG)Clinically significant change in total cholesterol, HDL-C, VLDL-C, and triglycerides from baselineHematological disorders with recent onset, defined as: decreased lymphocyte count < 500/mm3 (or < 0.5 × 109/l); decreased neutrophil count < 500/mm3 (or < 0.5 × 109/l); decreased platelet count < 30,000/mm3 (or < 30.0 × 109/l); and anemia with decreased Hb < 7.0 g/dl (or < 4.35 mmol/l)Hepatic adverse events (increase in ALT or AST > 3 times the ULN or baseline values or total bilirubin > 2 times the ULN or baseline values or suspected hepatocellular or cholestatic hepatotoxicity)Renal adverse events e.g. confirmed increase in serum creatinine ≥ 1.5 times the ULN or baseline values; a clinically significant decrease in creatinine clearance; a clinically significant increase in serum urea; and new onset of proteinuria

### Exploratory efficacy endpoints [timepoints: pre-pellet insertion assessment, 3 and/or 6 months after gestrinone or placebo pellet insertion]

Exploratory efficacy endpoints are defined as:Median participant satisfaction (ranging from 1 to 5, from very satisfied to very dissatisfied) – assessmentMedian intensity of pelvic pain and dysmenorrhea assessed by the VAS scaleProportion of participants who used medication to relieve pelvic painMedian number of days that participant used medication to relieve pelvic painChange in uterine bleeding patternProportion of participants with a change in Health-related Quality of Life measured with the 36-item Medical Outcomes Study Health Survey Form (SF-36)Average change in total score and score for each domain of the 36-item Medical Outcomes Study Health Survey Form (SF-36)Proportion of participants with changes in the Endometriosis Health Profile 30 (EHP- 30 The Endometriosis Health Profile) scoreAverage change in the total score and the score of each domain of the Endometriosis Health Profile 30 (EHP- 30 The Endometriosis Health Profile)

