### Assessment of outcomes measures

Outcomes measures will be assessed during each of the three study visits in the main study protocol (randomized, double-blind, parallel, placebo-controlled stage), including a baseline visit (pre-treatment), a 3-month visit and 6-month visit. A trained team, including a gynecologist, will conduct the study in the outpatient setting in all study centers. Clinical assessments, monitoring of adverse events, evaluation of androgenization (hirsutism, clitoral index, acne, alopecia, and deepening of the voice), as well as pelvic pain intensity and quality of life assessed by SF-36 questionnaire will be evaluated at all the three study visits. Laboratory blood assessment will be conducted at the baseline visit and in the 3-month visit and include: complete blood count, liver and kidney function (AST, ALT, alkaline phosphatase, urea, creatinine, and uric acid), lipid profile (triglycerides, total cholesterol, HDL, LDL, VLDL) and blood glucose, coagulogram (PT and aPTT), and plasma hormone levels (total testosterone, free testosterone, and SHBG). Quality of life assessment by the EHP-30 questionnaire will be applied at the baseline visit and in the 3-month visit. Data on uterine bleeding pattern and use of medication to relieve pelvic pain will be remotely collected using and electronic diary available at the App used in the study protocol.

Outcomes measures in the EXT-PK (open-label) will be assessed during each of the four study visits in which clinical evaluation, monitoring of adverse events, evaluation of androgenization, pelvic pain intensity and quality of life by SF-36 questionnaire will be conducted in each of the clinical visits, including baseline (pre-treatment), 1-month, 3-month, and 6-month after the insertion of gestrinone subdermal bioabsorbable pellet. Blood sampling for PK study will be conducted: pre-insertion of the gestrinone pellet (predose); different times after insertion of the gestrinone pellet: +24h; 7, 14, 21, 28, 56, 84, 112, 140, 168 days. Data on uterine bleeding pattern and use of medication to relieve pelvic pain will be remotely collected using an electronic diary established to be available at the App established to be used in the study protocol.

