### Study procedures

Participant-reported outcomes will be collected *via* the App used in the study protocol: Quality of Life 36-item Form Health Survey (SF-36); endometriosis health profile – Endometriosis Health Profile 30 (EHP-30); diary to record the use of analgesics for pelvic pain and uterine bleeding pattern. On the first visit, access to the App will be provided to the participant; the participant will receive guidance on how to use the App, and baseline data will be collected. Following the study procedure schedule, participants will receive reminders through the App to record outcomes, and telephone contact will be made for those who do not complete the form regularly. At follow-up visits, participants will be retrained if they present difficulties in using it.

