### Patient satisfaction with treatment

Participants must rate their satisfaction with the treatment by choosing one of the following alternatives presented in written form (ranging from 1 to 5): very satisfied, satisfied, not sure, dissatisfied, or very dissatisfied.

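### Satisfaction is to be compared with placebo, but the plan fixes a median of a five-level item and names only paired, baseline-referenced tests, which cannot make that comparison

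*Protocol article*

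**What the plan says.** Under Other exploratory objectives, the protocol article sets out to compare the gestrinone pellet with the placebo pellet on several outcomes, and participant satisfaction is among them. The objective is therefore a comparison between arms.

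The endpoint list defines the measure as "Median participant satisfaction (ranging from 1 to 5, from very satisfied to very dissatisfied"). A lower value means a more satisfied participant. The list stands under one shared heading, "Exploratory efficacy endpoints [timepoints: pre-pellet insertion assessment, 3 and/or 6 months after gestrinone or placebo pellet insertion".

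The section Patient satisfaction with treatment describes the instrument: "Participants must rate their satisfaction with the treatment by choosing one of the following alternatives", with five written options from very satisfied to very dissatisfied.

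The Statistical analysis section names two kinds of test. Scores and indices are compared with their pre-treatment values by a paired t-test and a Wilcoxon test. Changes in laboratory measurements and other secondary outcomes are compared by a paired Wilcoxon test. All tests are two-sided at 0.05 without multiplicity adjustment. The section also promises descriptive summaries by treatment group, with categorical variables given as proportions per category. It names no test between arms.

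**The concern.** The objective, the endpoint and the analysis do not fit together for this item. The objective asks whether the arms differ. The tests compare a participant with her own earlier value. The item rates satisfaction with a treatment that has not been given at the pre-insertion assessment, so there is no earlier value to pair with.

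If the paired test is set aside, what remains is one median per arm. With five levels, the median changes only when the cumulative 50% point moves into another category. Two arms can then report the same figure although many more participants are satisfied in one of them. Two nearly identical arms can also report different figures because they lie just on either side of 50%. At stake is whether a comparison that the trial promises can be read from the result it plans to report.

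**Working it through.** **1. The sections side by side.**

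| Element | What is stated | Fits a comparison with placebo? |
|---|---|---|
| Objective | Gestrinone versus placebo on satisfaction | Yes |
| Endpoint | Median of a 1–5 item | Only as two medians, with no effect measure or interval |
| Test for scores and indices | Paired, against pre-treatment | No: within participant, and no baseline exists |
| Test for laboratory changes and other secondary outcomes | Paired Wilcoxon | No: paired, and satisfaction is exploratory |
| Descriptive summaries by group | Proportions per category | Partly: shows the spread, but gives no comparison |

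The article states no power, effect size or expected distribution for satisfaction, so there is no figure of the plan's own to reproduce.

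**2. Inputs for the illustration.** From the document: 100 participants randomised 1:1, so 50 per arm; a possible 10% dropout (Discussion), so 100 × 0.9 / 2 = 45 per arm; two-sided 0.05. Assumed: the response distributions over levels 1 to 5. The main case is gestrinone 30/45/15/6/4% and placebo 12/43/22/13/10%.

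- Satisfied or very satisfied: 30 + 45 = 75% v 12 + 43 = 55%.
- Cumulative shares at levels 1 and 2: 30%, 75% v 12%, 55%. Both arms pass 50% at level 2, so both population medians are 2.
- Probability that a gestrinone participant is the more satisfied, ties split, is the sum over i of a_i × (sum of b_j for j > i, plus b_i / 2) = 0.30 × 0.94 + 0.45 × 0.665 + 0.15 × 0.34 + 0.06 × 0.165 + 0.04 × 0.05 = 0.644. No difference would give 0.50.

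**3. How often the sample medians agree.** At 50 per arm the median is 2 when at least 26 ratings are 1 or 2 and at most 24 are 1.

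- Placebo: P(Bin(50, 0.55) ≥ 26) = 0.716; the second condition almost never fails.
- Gestrinone: about 0.997.
- Both medians equal to 2: 0.716 × 0.997 = 0.714. Other ways of agreeing add almost nothing.

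So the medians are equal in about 71% of trials; simulations of 4,000 trials scatter between 70% and 72%. At 45 per arm the share is about 75%. A two-sided Wilcoxon rank-sum test on the same simulated data rejects in about 76% of trials at 50 per arm and about 71% at 45. In about 49% of trials at 50 per arm, the medians are identical and the rank-sum test is significant.

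**4. Sensitivity to the assumed distributions, 50 per arm.**

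| Gestrinone v placebo (%) | Population medians | Satisfied or very satisfied | Equal sample medians | Rank-sum power |
|---|---|---|---|---|
| 30/45/15/6/4 v 12/43/22/13/10 | 2 v 2 | 75% v 55% | 71% | 76% |
| 45/40/5/5/5 v 10/45/15/20/10 | 2 v 2 | 85% v 55% | 51% | 99% |
| 35/40/10/10/5 v 15/45/15/15/10 | 2 v 2 | 75% v 60% | 88% | 64% |
| 40/35/10/10/5 v 10/20/30/25/15 | 2 v 3 | 75% v 30% | under 0.2% | over 99% |
| 20/32/18/20/10 v 20/28/22/20/10 | 2 v 3 | 52% v 48% | 38% | about 5% |

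In the first three rows the median tends to miss a difference, and in the fourth it shows one. In the last row the sample medians differ in 100 − 38 = 62% of trials although the arms are almost alike.

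**5. What the proposed effect measure would deliver.** In the main case the difference in proportions is 0.75 − 0.55 = 0.20. Its 95% half-width at 50 per arm is 1.96 × √(0.75 × 0.25/50 + 0.55 × 0.45/50) = 1.96 × 0.0933 = 0.18. The interval is wide, but it shows direction and size, which two equal medians do not.

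**The case against.** The best defence is that nothing says outright that satisfaction will be tested against baseline. The Statistical analysis section speaks of scores and indices without naming this item. The endpoint is worded as a plain median, whereas some SF-36 and EHP-30 endpoints are worded as average changes. The pre-insertion time point stands in a heading shared by nine endpoints and worded with and/or, so it need not apply to each of them. This is fair, but it only removes the misfitting test. It supplies no test that serves the objective.

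A second defence is that a median is a conventional summary of an ordinal item, and that proportions per category by group are promised as well. This also stands in part: if those proportions are reported for satisfaction, a reader can see the spread. They remain descriptive, and the endpoint itself is still the median.

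A reader might go further and infer that satisfaction is never collected, because neither the itemised visit list nor the App list names it. The documents do not support that. The instrument has its own section and is presented in written form, which is compatible with collection outside the App. Assessment of outcomes measures opens with "Outcomes measures will be assessed during each of the three study visits in the main study protocol", and the endpoint heading gives 3 and/or 6 months. Which visit applies is a detail that a condensed article commonly leaves to the full protocol.

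A reader might also infer that the median will hide a large difference. It can, but the fourth row of the table shows it need not, and the document gives no distributions from which to say which case applies.

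**Conclusion.** The concern holds as a mismatch between objective and analysis. The plan promises a comparison with placebo on satisfaction, fixes a coarse summary for it, and names only tests that compare with a baseline this item cannot have.

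The size rests on assumptions. With 75% v 55% satisfied or very satisfied, the planned summary shows no difference between arms in about 71% of trials at 50 per arm (75% at 45), against about 76% power (71% at 45) for a rank-sum comparison of the same data. Other plausible distributions give results from near-certain agreement of the medians to near-certain disagreement, and the medians may also separate when the arms hardly differ.

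The importance is low. Satisfaction is exploratory in a trial whose primary and secondary outcomes concern safety, and its place at the head of the list is not said to give it rank. The absence of a named visit is something to confirm in the full protocol and is not part of this finding.

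**What to change.** State in the analysis section that:

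- satisfaction has no pre-insertion value and is exempt from the baseline-paired tests;
- the arms are compared on the post-insertion ratings over all five levels, by a Wilcoxon rank-sum test or a proportional-odds model;
- the between-arm difference in the proportion satisfied or very satisfied is reported with its 95% CI, beside the full distribution by arm;
- the median is kept as a descriptive summary.

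The full protocol should be checked for the visit or visits at which the item is rated, so that the comparison names its time point. The last visit was estimated for April 2025, so the wording should be fixed before unblinding if that has not yet happened. The cost is about one analysis sentence. No new data are needed, and neither treatment nor sample size changes.
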